## 4. Medications in clinical study

### 4.1 Overview of study medication

#### 4.1.1 Study medication

- Name: Futhan IV
- Active principal: nafamostat mesilate
- Dose: nafamostat mesilate 10 or 50mg/vial
- Character: white powder in clear vial
- Storage: at room temperature (1~30℃)
- Volume of active principal
  - 10mg of nafamostat mesilate in IV futhan
  - 50mg of nafamostat mesilate in IV futhan 50
- Effect:
  - ① Relieve acute symptom of pancreatitis (acute pancreatitis, acute phase of chronic pancreatitis, post-Op acute pancreatitis, acute pancreatitis after pancreatic duct imaging, traumatic pancreatitis)
  - ② Disseminated intravascular coagulation
  - ③ Anticoagulation of extracorporeal circuit on patients with hemorrhagic disease or tendency
- Dosage
  - (1) Administration
    - ① To relieve acute symptom of pancreatitis
      - : Generally, 10mg of nafamostat mesilate is dissolved in 500mL of 5% glucose fluid and administered intravenously for 2 hours once or twice daily. Decrease or increase on symptom.

② DIC

: 0.06~0.20 mg/Kg of nafamostat mesilate is dissolved in 1,000mL of 5% glucose fluid and administered intravenously for 24hours continuously.

③ To anticoagulate the extracorporeal circuit on patients with hemorrhagic disease or tendency

: For priming, two vials of nafamostat mesilate were dissolved in 2 mL 5% glucose fluid and mixed with 1000 mL normal saline. After carefully removing air bubbles from the circuit with the prepared fluid, nafamostat mesilate was dissolved with 15 mL of 5% glucose fluid and loaded into the anticoagulation line with a starting dose of 20~50 mg/hr. In clinical study, average dose of maintenance was 35mg/hour.

(2) Making IV fluids

To properly administer nafamostat mesilate, IV fluid should be prepared in following order.

① To relieve acute symptom of pancreatitis

① Add more than 1mL of 5% glucose fluid in 10mg nafamostat mesilate vial and dissolved fully.

② Mix fully dissolved fluid into 500mL of 5% glucose fluid.

② DIC

① Add more than 1mL of 5% glucose fluid in 10mg vial and more than 5mL of 5% glucose fluid in 50mL vial until fully dissolved.

② Mix fully dissolved fluid into 1,000mL of 5% glucose fluid.

③ To anticoagulate the extracorporeal circuit on patients with hemorrhagic disease or tendency

① For priming

i ) Add more than 1mL of 5% glucose fluid in 10mg vial and more than 5mL of 5% glucose fluid in 59mL vial until fully dissolved.

ii) Add containing 29mg of nafamostat mesilate into 500mL of normal saline.

② Extracorporeal circulation

i ) Add more than 1mL of 5% glucose fluid in 10mg vial and more than 5mL of 5% glucose fluid in 59mL vial until fully dissolved.

ii) dilute mixed fluid with the 5% glucose fluid to fit the capacity of anticoagulant continuous infuser.

④ Caution during dissolution

: Do not apply normal saline or mineral salts into the vial directly due to crystal formation.

#### 4.2 Production and packing of medication used in clinical study

The medication used in clinical study is produced by the study client and supplied to the pharmacist of the study institution.

The labeling of the medication followed the pharmaceutical article 71 section 5 and the contents are following.

1. Mark as “for clinical study”
2. Code name of medication
3. Production number and expiration date
4. Storage method
5. Company name of manufacturer or importer
6. Mark as “Use for clinical study only”

Clinical study labels should be attached at vial and outer packing.

#### 4.3 Maintenance and revocation of double blind status

This study is open label clinical study, thus revocation is not required.

## 5. Target disease and clinical study period

### 5.1 Target disease

Patients in ICU who are in need of CRRT with hemorrhagic tendency which restrains use of heparin

### 5.2 Clinical study period

12 months after approval of clinical study

## 6. Inclusion/exclusion criteria, target number of subjects and its estimation basis

### 6.1 Inclusion criteria

Patients are selected as subjects with following conditions;

- (1) Adult male/female patients aged from 18 to 80.
- (2) ICU patients who are hemodynamically unstable to be in need of CRRT and has one of the hemorrhagic tendencies described as follows.
  - ① Platelet < 100,000
  - ② aPTT > 60 sec
  - ③ PT-INR > 2.0
  - ④ Active bleeding
  - ⑤ Major surgery within 48 hours
  - ⑥ History of cerebral hemorrhage or major bleeding within 3 months
  - ⑦ Septic shock or DIC
- (3) Patients or his/her legal guardian has voluntarily agreed to participate in the study and provided written informed consent.

### 6.2 Exclusion criteria

Patients with following conditions are excluded;

- (1) Pregnancy, breast feeding or possibility of pregnancy
- (2) History of allergy to nafamostat mesilate that might lead to shock.
- (3) Any other conditions that made the candidate unfit according to the attending physician.

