## 9. Precautions using study medication

### 9.1 Precaution considering the study medication: SK chemicals corp. 'IV futhan'

#### 1. Warning

The patient should be inspected thoroughly to reveal any history of hypersensitivity, because of the concerns for shock or anaphylactoid reaction. Also, in case of a shock, prepare for emergency treatment, observe, and if these symptoms occur, immediately stop administering the medication and treat properly.

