#### 2. Prohibited in following patients

The patients who have history of hypersensitivity by the medication

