#### 3. Adverse events

##### (1) Improvement of acute symptom in pancreatitis

117 (1.74%) out of 6,732 cases showed adverse events. The symptoms included 55 cases (0.82%) of liver function abnormalities including GOT/GPT elevation, 23 cases (0.34%) of hypersensitivity reactions such as rash, urticaria, and 14 cases (0.31%) of electrolyte imbalance such as hyperkalemia. (Re-examination conclusion report result in Japan)

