##### (2) DIC

241 (6.69%) out of 3,602 cases showed adverse events. The major symptoms included 185 cases (5.14%) of electrolyte imbalance such as hyperkalemia and hyponatremia, 53 cases (1.47%) of liver function abnormalities, and 11 cases (0.31%) of hypersensitivity reaction. (Re-examination conclusion report result in Japan)

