##### (3) Anticoagulation of extracorporeal circuit in patients with hemorrhagic tendency

48 (1.18%) out of 4,053 cases showed adverse events. The major symptoms included 41 cases (1.01%) of gastrointestinal symptom, and 9 cases (0.22%) of hypersensitivity reaction. (Re-examination conclusion report result in Japan)

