##### (4) Severe adverse events

###### ① Shock, anaphylactoid reaction

Detailed observation is required due to possibility of shock and anaphylactoid reaction (respiratory distress, asthma-like reaction). And if these symptoms appear, immediate discontinuation of medication with proper management is required.

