###### ② Hyperkalemia

(Pancreatitis: 0.19%, DIC: 4.53%, anticoagulation for extracorporeal circuit: 0.02%; Re-examination conclusion report result in Japan)

Extra caution is required due to possibility of hyperkalemia, when using potassium sparing diuretics, potassium containing medication. When it occurs, immediate

discontinuation of the medication and proper management should follow. Also, there have been some cases of arrhythmia due to hyperkalemia.

(5) Other adverse events

- ① Skin: Occasionally rash, rarely erythema, urticaria occurred, and the medication is discontinued after the symptom appears.
- ② Musculoskeletal: Myalgia and arthralgia have been reported.
- ③ Gastrointestinal: Anorexia, diarrhea, nausea, vomiting have been reported.
- ④ Hepatobiliary: Occasionally GOT/GPT elevation, ALP elevation, LDH elevation, total bilirubin elevation and Jaundice have occurred.
- ⑤ Hematologic: Occasionally leucopenia, eosinophilia, thrombocytopenia, and thrombocytosis have occurred. Bleeding tendency can occur, and in this occasion, medication dose will be tapered or discontinued.
- ⑥ Cardiovascular: Palpitation, hypertension and hypotension can occurred.
- ⑦ Urologic: Intermittently BUN/Creatinine elevation occurred.
- ⑧ Systemic: Headache, chest pain, general weakness, chest discomfort, and rarely fever have been reported.
- ⑨ Administration site: Rarely pain and angiitis with swelling occurred.

4. General precaution

- (1) Hyperkalemia and hyponatremia due to potassium excretion inhibition and sodium excretion acceleration can be occurred. Hence serum potassium and sodium level should be checked regularly and if any abnormalities have been observed, immediate discontinuation and proper management should be performed.
- (2) When using Potassium containing medication and potassium sparing diuretics in combination, be cautious about hyperkalemia. Also, when abnormal serum potassium level is confirmed, electrocardiography should be checked to identify arrhythmia. When used in extracorporeal circuit, this medication can aggravate hemorrhage. Hence close observation is required, and if needed, the medication should be tapered or discontinued

5. Administration to elderly

Elderly are generally with reduced physiologic function and careful caution for dose reduction is required.

6. Administration to pregnant or lactating female

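### Exclusion (2) can be read as narrower than the protocol's own contraindication to nafamostat, and the minimum allergy record falls short of the history that section 9.1 asks for (minor)

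*Protocol*

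**What the plan says.** - **Eligibility.** Section 6.2, exclusion (2), and the same line in the Study Protocol Summary: "History of allergy to nafamostat mesilate that might lead to shock". Exclusion (3) lets the attending physician exclude any other unfit candidate.
- **Contraindication.** Section 9.1 item 2 lists those in whom the drug is prohibited: "The patients who have history of hypersensitivity by the medication".
- **Warning.** Section 9.1 item 1: "The patient should be inspected thoroughly to reveal any history of hypersensitivity, because of the concerns for shock or anaphylactoid reaction".
- **What counts as hypersensitivity.** Section 9.1 item 3 reports "23 cases (0.34%) of hypersensitivity reactions such as rash, urticaria" in pancreatitis, "11 cases (0.31%) of hypersensitivity reaction" in DIC and "9 cases (0.22%) of hypersensitivity reaction" in extracorporeal use. Shock and anaphylactoid reaction have their own entry under severe events: "Detailed observation is required due to possibility of shock and anaphylactoid reaction". Among other adverse events, under skin: "Occasionally rash, rarely erythema, urticaria occurred, and the medication is discontinued after the symptom appears".
- **Route to randomisation.** Section 8.2.9 checks suitability against 6.1 and 6.2. Sections 7.5 and 8.2.10 randomise patients who meet those criteria. Section 8.3.2 goes from the suitability check to the randomisation number to dosing. None of these four sections names 9.1.
- **Allergy history.** Section 8.2.2 lists what the history must contain and attaches a 2-year look-back to allergy. Section 8.3.1 takes past and current history at screening with no look-back.

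**The concern.** The protocol has two statements about who should not receive nafamostat, and they may not describe the same patients. The broader one is in the precautions for using the drug. The one that can be read as narrower is the one that decides who is randomised.

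Take a candidate who once had a rash or urticaria from nafamostat. On the restrictive reading of exclusion (2) this candidate is eligible, yet 9.1 item 2 forbids the drug. If 9.1 is applied only after allocation to futhan, the patient cannot have the allocated treatment, and this departure can arise in one arm only. If 9.1 is overlooked, a hemodynamically unstable patient receives a contraindicated drug.

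The record required by 8.2.2 adds a smaller gap. A reaction three years ago, even a shock-type one that exclusion (2) clearly covers, lies outside the period that must be documented.

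**Working it through.** **Text comparison**

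1. Exclusion (2) carries a qualifier about shock; 9.1 item 2 carries none.
2. Section 9.1 does not equate hypersensitivity with shock. Its pancreatitis count gives rash and urticaria as examples, and shock and anaphylactoid reaction are listed separately. So if the qualifier restricts, the group excluded by 6.2 is smaller than the group prohibited by 9.1.
3. The skin entry, which stops the drug when a rash appears, is about management during treatment. It shows that skin reactions are taken seriously, but it does not define which history excludes a patient.
4. The operative steps (7.5, 8.2.9, 8.2.10, 8.3.2) point to the section 6 criteria, so the wording of 6.2 decides randomisation unless the physician uses exclusion (3) or applies 9.1 beforehand.
5. The required allergy record in 8.2.2 covers 2 years; the history sought in 9.1 item 1 has no limit.

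**Size**

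Inputs: hypersensitivity counts and treated cases from 9.1 item 3; 66 planned patients, 33 per arm, from 6.3.1. The protocol does not say how many candidates had nafamostat before, so prior exposure *e* is an assumption with range 0% to 100%. The reaction rate per treated case stands in for the prevalence of a past reaction among exposed candidates.

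Formula: expected number = *N* × *e* × (reactions / treated cases).

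The protocol's percentages reproduce: 9/4,053 = 0.22%, 11/3,602 = 0.31%, 23/6,732 = 0.34%.

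| Source in 9.1 | Treated cases per reaction | Expected in 66, *e* = 100% | Expected in 33 (futhan arm), *e* = 100% |
|---|---|---|---|
| Extracorporeal circuit | 4,053/9 = 450 | 66 × 9/4,053 = 0.147 | 33 × 9/4,053 = 0.073 |
| DIC | 3,602/11 = 327 | 66 × 11/3,602 = 0.202 | 33 × 11/3,602 = 0.101 |
| Pancreatitis | 6,732/23 = 293 | 66 × 23/6,732 = 0.225 | 33 × 23/6,732 = 0.113 |

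At *e* = 0% every entry is 0. The range is therefore 0 to 0.23 in the whole trial and 0 to 0.11 in the futhan arm.

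At *e* = 100% the chance of at least one such patient among 66, 1 − (1 − rate)^66, is 13.6%, 18.3% and 20.2% for the three rates.

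Under this proxy these are upper ends. The counts may include shock-type reactions that exclusion (2) already removes, and nothing is deducted for exclusion (3) or for 9.1 itself. They show the order of magnitude only.

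**The case against.** The strongest objection is that there may be no contradiction. The shock phrase can be read as the reason for excluding any nafamostat allergy. The warning in 9.1 item 1 supports this, because it joins the same two ideas as a precaution and its reason: "The patient should be inspected thoroughly to reveal any history of hypersensitivity, because of the concerns for shock or anaphylactoid reaction". Even as a restriction, the phrase looks forward to what re-exposure could cause, so a clinician could place an earlier rash within it. This stands: the wording leaves both readings open, and a reader who infers that 6.2 definitely admits patients with mild reactions goes further than the text allows. What remains is that an eligibility criterion with two fair readings, one of which conflicts with the contraindication, should be reworded.

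A second objection is that the protocol already deals with the risk. The prohibition in 9.1 binds, the warning orders an active search, history is taken at screening, and exclusion (3) is available. This also stands in large part. A reader might infer that the plan permits giving a contraindicated drug. It does not: doing so would breach 9.1. The safeguards make the event less likely, but they do not correct the criterion on which allocation rests.

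A third objection concerns the 2-year period. A reader might infer that 8.2.2 contradicts 9.1. It does not. The period appears in a list of contents that must be included, after an instruction to establish the history thoroughly, and nothing prevents asking further back. It is a minimum record that falls short of 9.1 item 1, not a rule that opposes it.

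**Conclusion.** The point holds as a minor safety and consistency correction. Exclusion (2) can be read as narrower than the prohibition in 9.1 item 2, and on that reading a patient could be randomised to a drug that the protocol forbids for that patient. The minimum allergy record in 8.2.2 is shorter than the history that 9.1 item 1 wants.

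The effect is rare: 0 to 0.23 patients expected among 66. That range rests on an assumed prior exposure of 0% to 100% and on reaction rates in treated cases as a proxy for a past reaction. A reader might infer an effect on the trial's numbers, but none follows: the sample size and the planned estimates are unchanged. Nor does the point bear on the rule in 11.3.1 that counts futhan patients only once they have been dosed. That is a separate matter which this correction would not resolve.

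**What to change.** 1. In section 6.2 and in the synopsis, reword exclusion (2) to *history of hypersensitivity to nafamostat mesilate*, so that it matches 9.1 item 2.
2. In section 8.2.2, add a question, to be answered before randomisation, about any earlier reaction to nafamostat, with no time limit. The 2-year period can stay for the rest of the history.

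The cost is one line in two places and one screening question. Under the proxy above, fewer than one additional screen failure is expected among 66 candidates (at most 0.23), even if all had received nafamostat before.

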### 6.3 Target number of subjects and its estimation basis

#### 6.3.1 Number of subjects

We are planning to enroll 33 subjects per group that is suitable for inclusion/exclusion criteria and analyze final group of 31 subjects.

|                                                      | Futhan group | No-anticoagulation group | Total subjects |
|------------------------------------------------------|--------------|--------------------------|----------------|
| Validity assessment subjects                         | 31           | 31                       | 62             |
| Validity assessment subjects including drop-out (5%) | 33           | 33                       | 66             |

### 6.3.2 Estimation basis

Primary end point of this clinical study is to evaluate the mortality of Futhan group and compare it to mortality of no-anticoagulation group.

Generally, the mortality of CRRT patients in ICU is known to be roughly 50% [1,4,5].

Thus, we anticipate the mortality in futhan group as 50% and assume the tolerance as 15% to estimate actual mortality. Also, we will add the same number of no-anticoagulation subjects to compare with futhan group on mortality.

Level of significance, ( $\alpha = 0.1$ )

Allowable limits of error for mortality are 15%. ( $\delta=0.15$ )

Considering the patient's severity in ICU, wastage rate is set at 5%. ( $r = 0.05$ )

Hence, necessary number of subjects is calculated after the following formula;

$$n_t = \frac{Z_{1-\alpha/2}^2 p(1-p)}{\delta^2}$$

By this formula, we estimate necessary number of subjects and calculate the final number of subjects by considering drop-out rate using the following formula.

$$n = \frac{n_t}{1-r}$$

The necessary number of subjects is 31 patients per group, and considering the 5% drop out rate, the final number would be 33 patients per group.

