#### 3.1 Purpose

##### 3.1.1 Primary end point

We are planning to compare mortality in ICU between nafamostat mesilate group and no-anticoagulation group in patients who are not fit to use heparin due to hemorrhagic tendency.

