## 7.5 Randomization

In this study, patients are randomly assigned to either futhan group or no-anticoagulation group and are proceeded as parallel study. Necessary subject number is 33 patients in each group, considering the wastage rate of 5%.

At the enrollment, patients are assigned randomly with stratification of diabetes mellitus. Patients who enrolled in the study was assigned to futhan group or no-anticoagulation group according to the random assignment number by preformed random place card.

If group A is futhan group, group B is no-anticoagulation group, vice versa.

The following is the example when block size is 4 or 6

List number of cases: 1=AABB, 2=ABAB, 3=ABBA, 4=BAAB, 5=BABA, 6=BBAA, 7=AAABBB, 8=AABABB, ..., 26=BBBAAA (26 number of cases)

SAS Random Program value (randomly assign 1 to 26): 1, 26, 8, 2, 1 ....

Random assignment order: AABB BBBAAA A ABABB ABAB AABB ....

Random assign number of subjects was assigned to the patients who fit the inclusion criteria and not the exclusion criteria in order of registration by the random place card that was pre-distributed to the researchers

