### 11.2 Assessment method

#### 11.2.1 Primary validity assessment variable

Mortality at ICU:

We will check whether patients' mortality at ICU after CRRT is 50% and additionally whether there is any statistically significant difference between two groups.

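### The 31-per-group size in 6.3.2 gives the stated 15% limit for each arm's mortality but does not size the between-group comparison that is the primary purpose, and 11.2.1 ranks that comparison behind a check against 50%

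*Protocol*

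**What the plan says.** The primary purpose (Protocol 3.1.1) is comparative: "We are planning to compare mortality in ICU between nafamostat mesilate group and no-anticoagulation group". Section 6.3.2 words the primary end point in two parts, evaluating mortality under Futhan and comparing it with the no-anticoagulation group.

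The calculation in 6.3.2 uses an anticipated Futhan mortality of 50% (the general figure for ICU patients on CRRT), alpha = 0.1, and a tolerance stated as "Allowable limits of error for mortality are 15" per cent. The formula is Z² at 1−α/2 times p(1−p), divided by δ²; it contains one proportion and no power term. The second arm enters by a sentence: "we will add the same number of no-anticoagulation subjects to compare with futhan group on mortality". The result is 31 evaluable and 33 enrolled per group. No control-arm rate, difference to detect, margin or power is given.

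For the primary variable, section 11.2.1 will check whether patients' "mortality at ICU after CRRT is 50% and additionally whether there is any statistically significant difference between two groups". Section 11.2.2 (1) and (2) repeats this order for hospital and 28-day mortality. Section 11.3.3.1 adds only that ICU mortality is presented.

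On allocation, section 7.5 says: "At the enrollment, patients are assigned randomly with stratification of diabetes mellitus".

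**The concern.** The question that justifies randomising is whether mortality differs between the arms. The only numerical justification for the size concerns how closely one arm's mortality is known. A difference between two independent proportions has the sum of their variances, so copying the first arm's number into the second does not carry the 15-point limit over to the difference.

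Section 11.2 widens the gap. It puts first a comparison with a fixed figure that is itself the planning assumption. Whether ICU mortality is near 50% reflects who was enrolled and how sick they were; it cannot show an effect of nafamostat, because the concurrent control group plays no part in it. The randomised comparison becomes the addition, which reverses the priority set in 3.1.1.

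At stake is the reading of the primary result. With death as the end point, a finding of no significant difference, or of mortality close to 50%, could be read as reassurance that a trial of this size cannot give.

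**Working it through.** **Inputs.** From 6.3.2: p = 0.50, δ = 0.15, two-sided α = 0.10 (Z = 1.645), drop-out r = 0.05, 31 evaluable per group. The 95% figures (Z = 1.960) use a level that the protocol did not choose and are shown for reference.

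**1. The plan's own figure.** 1.645² × 0.25 / 0.15² = 30.06, rounded up to 31. Then 31 / 0.95 = 32.6, rounded up to 33. Both stated numbers reproduce. A one-sided 0.10 level would give 19 and a two-sided 0.05 level 43, so the calculation is a 90% two-sided interval for one proportion.

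**2. Precision for each arm.** Half-width = Z × √(p(1−p)/n) = 1.645 × √(0.25/31) = 0.148. Because both groups have 31, each meets the 15-point limit.

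**3. Precision for the difference.** Half-width = Z × √(2p(1−p)/n), with 50% in both arms:
- 90%: 1.645 × √(0.50/31) = 0.209
- 95%: 1.960 × √(0.50/31) = 0.249
- 90% with all 33 per arm evaluable: 1.645 × √(0.50/33) = 0.202

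**4. Size for a 15-point limit on the difference (90%).** n = 1.645² × 0.50 / 0.15² = 60.1, so 61 per arm, or 61 / 0.95 = 64.2, so 65 with drop-out. This is about twice the plan.

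**5. Power, as an illustration only.** The protocol names no difference to detect and no test. Assume 50% v 35% and an uncorrected two-proportion test with pooled variance under the null:
- Null standard error: √(2 × 0.425 × 0.575/31) = 0.1256. Standard error under the alternative: √((0.25 + 0.2275)/31) = 0.1241.
- Two-sided 0.10: (0.15 − 1.645 × 0.1256)/0.1241 = −0.456, which gives 0.324; the opposite tail adds 0.002, so about 33%.
- Two-sided 0.05: the same steps give about 22%.
- Fisher's exact test under the same rates gives 23% (0.10) and 16% (0.05).
- About 80% power at 0.10 needs a fall from 50% to about 20% (81% uncorrected, 73% with Fisher's test).

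**6. What a check against 50% could show.** Section 11.2.1 does not say whether the check is a test or an estimate, nor whether it is made per arm or pooled. If it is an exact two-sided binomial test at 0.10, it does not reject 50% for:
- 11 to 20 deaths of 31 (35% to 65%), per arm
- 25 to 37 deaths of 62 (40% to 60%), pooled

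Non-rejection therefore fits a wide span of mortality rates and would not confirm 50%.

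**The case against.** The strongest reply is that 6.3.2 is coherent on its own terms. It attaches 15% to a mortality rate and never to the difference, brings in the control arm openly for comparison, and claims no power, margin or detectable difference. Its end point has an estimation part, which the size serves. All of that stands, and it limits the point in several ways.

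- A reader might infer that the sample-size arithmetic is wrong. It is not; 31 and 33 reproduce.
- A reader might infer that only the Futhan arm meets the limit. Both arms do, since both have 31.
- A reader might infer that the protocol promises 15-point precision for the comparison, or treats a null result as equal mortality. No section says either. The risk lies in a size presented as necessary with nothing said about the comparison.
- A reader might infer that the trial is underpowered for its own target. There is no target. The 35% is assumed here, and power shifts with that rate and with the test.
- A reader might infer that 11.2.1 fixes a hypothesis test of 50%. The wording would also fit an estimate with an interval, which is what 6.3.2 sizes, and 11.3.3.1 says only that mortality is presented.

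It can also be said that test and model details belong in the SAP, which is not shown. That is fair for the choice of method and for covariate adjustment. It does not answer the main point: the sizing basis and the order of the primary questions are both fixed in this protocol.

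**Conclusion.** The point holds as a mismatch between the sizing and the primary question, not as a calculation error. The planned 31 evaluable patients per group estimate each arm's mortality to ±14.8 points (90%), as intended, and the between-arm difference to ±20.9 points (90%) or ±24.9 points (95%). These figures rest only on the protocol's own 50%, applied to both arms, and the normal approximation; they carry the conclusion. The power of about 33% (two-sided 0.10) or 22% (0.05) depends on the assumed 50% v 35% and an uncorrected test, is lower with an exact test, and serves as illustration.

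That 11.2.1 and 11.2.2 (1)-(2) put a check against the planning value before the randomised comparison is plain from the text. The non-rejection ranges of 11 to 20 of 31, or 25 to 37 of 62, hold only if the check is an exact test at 0.10. On either reading, the check gives no evidence about nafamostat.

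**What to change.** - **Section 6.3.2:** keep 33 per arm. State that the 15% limit applies to each arm's mortality rate; that the between-arm difference is estimated to about ±21 points (90%) with 31 evaluable per arm and 50% mortality; that no power is claimed; and that a non-significant difference is therefore not evidence of equal mortality.
- **Sections 11.2.1 and 11.2.2 (1)-(2):** remove the check against 50%. Make the between-arm risk difference with its confidence interval the main result, analysed by the diabetes strata already used in randomisation (7.5).

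An analysis adjusted for APACHE II, which is collected at screening, is optional and not part of this correction.

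The cost is a few sentences in two sections and no extra patients. The change does not make the comparison more precise, and the stated precision will look less favourable than the present 15%. In return, the text describes what the trial can say about its own primary question.
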